### Statistical analysis

Parametric and nonparametric statistical tests will be applied using the SPSS version 16 (SPSS Inc., Chicago, IL, USA) and Stata/SE 10.0 (StataCorp Inc., College Station, TX, USA) for data analysis. Descriptive data will be analyzed for linearity and will be expressed as percentages, median and mean. The two groups will be compared for uniformity on sociodemographic variables, clinical manifestations and laboratory parameters at baseline. After completion, primary and secondary outcomes will be compared in the groups using statistical methods for comparison of means and using regression analysis. For each of the outcomes, multilevel regression analysis will be used to examine differences between trial arms. For binary outcomes the model will be logistic and for continuous outcomes the model will be linear regression. All analyses will follow intention-to-treat principles and a prespecified analysis plan. Where appropriate, sensitivity analyses will be conducted (for example, control for additional covariates; and bootstrapped *p* values for skewed outcomes). In the case of missing data values, we will apply mean imputation and regression imputation where rates are low, and consider multiple imputations where they exceed 10%. A *p* value < 0.05 will be considered significant.

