### Sample size

The sample size calculation was based on formulae for analysis between differences of means. The value for alpha was set at 0.05 and the value for 1 − beta was set at 0.9. Sample sizes were calculated for a difference of systolic blood pressure by 10 mmHg and diastolic blood pressure by 5 mmHg. Standard deviation values were taken as 18 mmHg for systolic blood pressure and 10.7 mmHg for diastolic blood pressure as per prior investigations on patients with resistant hypertension. Using the above parameters the calculated sample sizes were 140 and 180 patients to detect differences in systolic and diastolic blood pressures, respectively. Using the greater number and adjusting for dropout and noncompliance rates a sample of 200 patients will be recruited with a 1:1 allocation per group.

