### Study period

The study will be conducted for a period of 3 months. The visits and the evaluations will be done as follows: screening (visit 0), 1 month (visit 1), 2 months (visit 2) and 3 months (visit 3).

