### Outcomes

Primary outcomes: the primary outcomes of the study are to find a statistically significant difference between the fall in mean systolic and mean diastolic blood pressure measured by ABPM (ambulatory blood pressure monitoring) from baseline between the two groups.

Secondary outcomes:To determine the difference in cardiovascular outcomes, including acute coronary syndrome, acute stroke and acute heart failure, between groupsTo determine the variations in plasma and urinary electrolytes between the two groups at measured endpointsTo assess renal outcomes as measured by the glomerular filtration rate between groupsTo determine variations in plasma renin activity (PRA) and angiotensin:aldosterone ratios between the study groupsTo determine differences in oxidative stress between the study groups using nitric oxide as a surrogate markerTo assess safety outcomes, including the incidence of serious adverse effects, between the two groups at measured endpoints

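### Multilevel logistic regression is fixed for every binary outcome, but the cardiovascular events are likely to be too sparse for it to give a usable estimate

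*Protocol article*

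**What the plan says.** The Statistical analysis section states: "For each of the outcomes, multilevel regression analysis will be used to examine differences between trial arms". The next sentence assigns the model by outcome type: "For binary outcomes the model will be logistic and for continuous outcomes the model will be linear regression". Neither sentence makes an exception, and the section applies a 0.05 significance threshold throughout.

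The Outcomes section lists the binary outcomes that this covers. One secondary outcome is the between-group "difference in cardiovascular outcomes, including acute coronary syndrome, acute stroke and acute heart failure". Another is "safety outcomes, including the incidence of serious adverse effects". Safety is also named beside efficacy in the primary objective.

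The size and length of the trial come from two other sections: "a sample of 200 patients will be recruited with a 1:1 allocation per group" (Sample size) and "The study will be conducted for a period of 3 months" (Study period). Recruitment is from the clinics of one hospital. No event rate, and no power for any binary outcome, is stated.

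**The concern.** Logistic regression by maximum likelihood needs events in both arms. If one arm has none, the likelihood keeps rising as the log odds ratio goes to infinity. The software then stops at an arbitrary large value with a huge standard error, or reports non-convergence. The Wald p value tends to 1 whatever the count in the other arm.

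The multilevel part adds a second difficulty. For the clinical events there is one hospital and, in effect, one yes/no result per patient, so no clustering level is evident to carry a random effect. Repeated visits could supply a patient level for laboratory values. They hardly do so for an event that most patients never have.

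At stake is whether the trial can report an interpretable between-group estimate for its cardiovascular and serious-event outcomes. A secondary risk is that a failed fit, reported as a p value near 1, is taken as showing no difference.

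**Working it through.** **Inputs.** From the protocol: 200 patients at 1:1, so n = 100 per arm, and 3 months of follow-up, so 100 × 0.25 = 25 patient-years per arm. Assumed, because the protocol gives none: annual event rates r of 1%, 2%, 4% and 8%, equal in both arms. The protocol's own design figures concern blood pressure only, so there is no stated figure to reproduce here.

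**Step 1: chance of an empty arm.** The 3-month risk is p = 1 − exp(−0.25r). The chance that a given arm is empty is q = (1 − p)^100 = exp(−25r). Then:
- at least one arm empty = 1 − (1 − q)²
- both empty = q²
- exactly one empty = 2q(1 − q)

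| Annual rate | Expected events per arm | q | At least one empty | Both empty | Exactly one empty |
|---|---|---|---|---|---|
| 1% | 0.25 | 0.779 | 95.1% | 60.7% | 34.5% |
| 2% | 0.5 | 0.607 | 84.5% | 36.8% | 47.7% |
| 4% | 1.0 | 0.368 | 60.0% | 13.5% | 46.5% |
| 8% | 2.0 | 0.135 | 25.2% | 1.8% | 23.4% |

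The step from 180 to 200 patients implies about 10% loss (20/200). With 90 per arm, the chance of at least one empty arm rises to 96%, 87%, 65% and 30%. At a 3-month risk of 5% per arm, which pooled serious adverse effects might reach, it is only about 1% (100 per arm).

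**Step 2: what the model returns when one arm is empty.** An ordinary logistic fit to k/100 against 0/100, stopped after 25 iterations, gives a log odds ratio of about 23 to 24, a standard error of about 35,600 and a Wald p of about 0.999 for every k from 2 to 10. These values depend on when iteration stops. That the p value is near 1 does not.

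| Events | Wald p | Likelihood-ratio p | Fisher p |
|---|---|---|---|
| 3 v 0 | 0.999 | 0.040 | 0.25 |
| 5 v 0 | 0.999 | 0.008 | 0.059 |
| 6 v 0 | 0.999 | 0.004 | 0.029 |
| 8 v 0 | 0.999 | 0.0007 | 0.007 |

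**Step 3: how often a significant harm would be lost this way.** Fisher's test needs at least 6 v 0 to reach p < 0.05 against an empty arm. With 100 per arm, the chance of one empty arm and 6 or more events in the other is:
- 2% v 4% a year: 0.03%
- 4% v 8%: 0.6%
- 2% v 8%: 0.9%
- 1% v 8%, the widest contrast in the assumed range: 0.779 × P(6 or more of 100 at 1.98%) = 0.779 × 0.0148 = 1.2%
- 4% v 16%, outside the range: 7%

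The 8 v 0 row is also outside the range: 8% in 3 months is −ln(0.92)/0.25 = 33% a year.

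**Step 4: what a direct method returns.** Zero events in 100 patients has a two-sided exact upper limit of 1 − 0.025^(1/100) = 3.6%. For 2/100 v 0/100, the Wilson limits are 0.55% to 7.00% and 0% to 3.70%. The hybrid score interval for the risk difference of 2.0 points is therefore 2.0 − √(1.45² + 3.70²) = −2.0 to 2.0 + 5.0 = 7.0 points. The interval is wide, but it is finite and readable. Penalised logistic regression also stays finite: for 8 v 0 the odds ratio is 18.5 (95% CI 1.05 to 325), obtained by adding 0.5 to each cell.

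**The case against.** **The article is condensed and defers to an analysis plan that is not shown.** It also opens by promising both parametric and nonparametric tests, and it gives its sensitivity analyses only as examples. This has weight: a missing sparse-data fallback alone would be no finding. But the article goes further and commits each outcome to a named model, so an exact method in the plan would depart from the published text. The sensitivity analyses it names do not help. Extra covariates make sparsity worse, and a bootstrap of an empty arm always returns an empty arm.

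**The event rates are assumed.** This stands. An empty arm is likely at 3-month risks up to about 1% per arm, still a one-in-four chance at 2%, and rare at 5%. Pooled serious adverse effects may fit without trouble.

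**The protocol does not prescribe a Wald test.** This also stands in part. A likelihood-ratio test from the same model gives a p value, but it supplies no finite odds ratio and is anti-conservative at small counts (0.040 against Fisher's 0.25 for 3 v 0).

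**A reader might infer that the plan would often hide a real harm.** The documents and the figures do not support that. Within the assumed rates, a Fisher-significant result against an empty arm has a chance of about 1% or less; usually neither test would be significant. The larger percentages in Step 1 count empty arms, not lost signals. Nor does the protocol say that a non-significant result will be reported as evidence of safety. The Adverse effect evaluation section provides for documentation, reporting of serious events and review by an independent monitoring board. That protects patients during the trial, but it does not mend the published comparison.

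**Conclusion.** The concern holds in a limited form. The protocol fixes multilevel logistic regression for all binary outcomes, and for the individual cardiovascular events this is a poor choice at 100 patients per arm over 3 months. At assumed annual rates of 1% to 8%, at least one arm is empty in 95% down to 25% of trials. In about 23% to 48% exactly one arm is empty, so the odds ratio has no finite estimate and its Wald interval and p value are uninformative. In 61% down to 2% both are empty and no model can be fitted.

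The consequence is an unusable estimate and interval, not a significant harm frequently missed. The ambulatory blood pressure primary outcomes and the sample size are unaffected. The conclusion rests on the assumed rates and weakens as events become more common. This is a cheap improvement, not a fault that threatens the trial.

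**What to change.** For the cardiovascular events and serious adverse effects, replace the multilevel logistic model with:
- the number of patients with an event in each arm
- the risk difference with an exact or score 95% confidence interval
- Fisher's exact test, with Firth-penalised logistic regression if a model is wanted.

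Add a sentence that a non-significant result for these outcomes will not be interpreted as evidence of no difference.

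The cost is a few sentences and slightly more programming, with no extra patients. The Trial status section says that enrolment has not started, so the change can be made before any data exist. The downside is that covariate adjustment is lost for these outcomes.

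### Single (mean or regression) imputation is prescribed at low missingness with no exemption for the primary ABPM outcome; depending on the version, it makes standard errors too small or shrinks the treatment effect

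*Protocol article*

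**What the plan says.** The Statistical analysis section of the protocol article states the missing-data rule in one sentence: "we will apply mean imputation and regression imputation where rates are low, and consider multiple imputations where they exceed 10" per cent. It applies to missing values in general. The section does not set the primary ABPM outcome apart, say which of the two single-imputation methods applies to which variable, or say whether the mean is overall or within arm. A p "value < 0.05 will be considered significant". Outcomes are to be analysed by intention to treat, with comparisons of means and with multilevel regression.

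The Sample size section calculates 140 patients for systolic and 180 for diastolic pressure, takes the larger, and says that "adjusting for dropout and noncompliance rates a sample of 200 patients will be recruited". It gives no attrition rate.

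The Study schedule section lists 24-h ABPM at the enrolment visit. For visits 1 and 2 it lists office pressure, pulse, blood tests and an electrocardiogram, but no ABPM. Fig. 2, which holds the full schedule, is not shown.

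**The concern.** Single imputation puts a made-up value in each gap, and the analysis then treats it as measured. A value equal to the arm mean, or lying exactly on a regression line, adds no scatter but counts as a patient. The residual variance falls, the apparent sample size rises, and the standard error comes out too small. A value equal to the mean over both arms pulls the two arms together and shrinks the difference.

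The rule as worded governs the primary estimate, its confidence interval and its p value. Because it leaves the type of mean open, the analyst could choose between a version that overstates significance and one that understates the effect. Above 10% missing, multiple imputation is only considered, so single imputation is not ruled out there either.

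**Working it through.** **Inputs (Sample size section).** "The value for alpha was set at 0.05"; sidedness is not stated, so two-sided is assumed. Power: "the value for 1 − beta was set at 0.9". Target effects: "a difference of systolic blood pressure by 10 mmHg and diastolic blood pressure by 5 mmHg". Standard deviations: "18 mmHg for systolic blood pressure and 10.7 mmHg for diastolic blood pressure". Stated totals: "the calculated sample sizes were 140 and 180 patients", raised to 200.

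**The plan's own figures.** Per arm, n = 2[SD(1.960 + 1.282)/difference]².
- Systolic: 2(18 × 3.242/10)² = 68.1, so 69 per arm and 138 in total. This agrees with 140.
- Diastolic: 2(10.7 × 3.242/5)² = 96.2, so 97 per arm and 194 in total, against 180 stated. This does not reproduce. It is a separate matter and nothing below depends on it.
- Allowance: 180/(1 − 0.10) = 200, so the implied loss is 20/200 = 10%. It covers dropout and noncompliance together.

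**Arm-mean imputation.** Let a fraction m be missing completely at random in each arm of n = 100.
- True SE of the difference = SD√[2/(n(1 − m))]. At m = 0.10 and SD 10.7 this is 1.595.
- SE the analysis reports ≈ SD√[2(1 − m)/n] = 1.436.
- The ratio is 1 − m = 0.90, so type I error = 2[1 − Φ(1.96 × 0.90)] = 7.8%. At m = 0.05 it is 2[1 − Φ(1.96 × 0.95)] = 6.3%.

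**Overall-mean imputation.** The effect is multiplied by 1 − m. A difference of 5 mmHg becomes 4.75 at 5% missing and 4.5 at 10%; 10 mmHg becomes 9.5 and 9.0.

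**Simulation check.** 20,000 trials per setting, 100 per arm, SD 10.7, missing completely at random and equally by arm. Regression imputation used arm and a baseline value with an assumed correlation of 0.5, followed by a baseline-adjusted analysis.

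| Method | Type I error, 5% missing | Type I error, 10% missing | Mean estimate of a true 5 mmHg, 10% missing | 95% CI coverage at a true 5 mmHg, 10% missing |
|---|---|---|---|---|
| Complete cases | 5.0% | 4.9% | 4.99 | 95.0% |
| Arm mean | 6.2% | 7.8% | 4.99 | 92.2% |
| Regression, adjusted analysis | 6.3% | 7.7% | 4.99 | 92.1% |
| Overall mean | 5.0% | 4.9% | 4.49 | 93.6% |

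**Regression imputation followed by a plain comparison of two means.** The protocol also names comparison of means. If the predictors explain a share R² of the outcome variance (not given in the document, so a range is shown), the ratio of reported to true SE is about √{[R² + (1 − R²)(1 − m)] / [R² + (1 − R²)/(1 − m)]}. For R² = 0.25 and m = 0.10 this is √(0.925/1.083) = 0.924, which gives 7.0%.

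| R² | 5% missing: formula (simulated) | 10% missing: formula (simulated) |
|---|---|---|
| 0.25 | 5.9% (5.9%) | 7.0% (6.9%) |
| 0.50 | 5.6% (5.6%) | 6.3% (6.4%) |
| 0.70 | 5.4% (5.3%) | 5.8% (5.7%) |

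The simulated values come from 40,000 trials with 100 per arm. Over both analysis models, regression imputation gives about 5.3% to 7.7%.

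**The case against.** Several points on the other side are fair, and they limit the size of the finding.

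- **The missing rate.** A reader might infer that the trial plans for exactly 10% missing ABPM values. The document does not support this. The 10% is derived from 180 and 200, and it includes noncompliance; under intention to treat, a noncompliant patient who attends visit 3 still contributes a reading. Missing ABPM is thus at most 10% under that allowance and probably less. The low-rate category is not defined either, although 10% is the only threshold given. The figures at 10% missing are the edge of the single-imputation branch.
- **Bias and false precision together.** A reader might infer that the rule both biases the estimate and understates its standard error. Under missingness completely at random, no version does both: the arm mean and regression imputation leave the estimate unbiased, and the overall mean leaves the type I error nominal.
- **Reasons for dropout.** It is tempting to assume that patients without a final ABPM stopped for side effects or poor control. The suspension criteria include serious adverse events but not poor control, and uncontrolled pressure is handled within the trial. Outcome-related dropout is plausible, but the document gives neither its rate nor its direction.
- **Multilevel regression.** Such a model can use incomplete repeated measures without imputation. But the text shows no ABPM at visits 1 and 2, so it does not clearly rescue the primary outcome, and the imputation rule is stated regardless.
- **Detail left to the analysis plan.** The choice of predictors, and any sensitivity analysis for missing data, can properly sit in the prespecified plan that the protocol mentions. The listed sensitivity analyses are only examples. The rule itself, however, is stated in the protocol, and an analysis plan that followed it would inherit it.

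**Conclusion.** The concern holds at moderate size. As written, the rule allows an invalid analysis of the primary outcome, and every version performs worse than leaving the gaps unfilled when data are missing completely at random. At 5% to 10% missing, the type I error is about 6.2% to 7.8% for the arm mean and 5.3% to 7.7% for regression imputation, or the effect is attenuated by 5% to 10% for the overall mean. The planned attrition would probably fall in this branch.

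These figures assume a two-sided 5% test, 100 per arm, equal missingness in both arms and missingness completely at random; the regression figures also rest on assumed predictor strength. Outcome-related dropout could add bias, but its size cannot be derived from the document. The point should be fixed. The demonstrated harm does not make it a fatal flaw.

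**What to change.** For the primary outcome, delete mean imputation, single regression imputation and the 10% switch. At any missing rate, use multiple imputation by arm, with baseline ABPM and the office pressure and pulse from visits 1 and 2 as predictors, or an equivalent likelihood-based model. Follow it with baseline-adjusted regression. The protocol already collects all of these measurements.

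Multiple imputation does not by itself remove bias from outcome-related dropout. A sensitivity analysis that worsens the imputed values in patients who stopped treatment would therefore be a useful optional addition; its absence is not an error in the protocol.

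The cost is a change of wording, a little more programming, and slightly wider confidence intervals because they then carry the uncertainty of the missing values. No patients, visits or measurements are added. The Trial status section says that enrolment has not started, so the change can be made before any data exist.

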### Adverse effect evaluation

Described adverse effects of propranolol include: aggravation of congestive heart failure, bradycardia, hypotension, arthropathy, Raynaud’s phenomenon, hyper/hypoglycemia, depression, fatigue, insomnia, paresthesia, psychotic disorder, pruritus, nausea, vomiting, hyperlipidemia, hyperkalemia, muscle cramps, bronchospasm, dyspnea, pulmonary edema and respiratory distress. In the event of a probable adverse reaction, the following precautions would ensure timely identification and management of patients:Reporting: mechanisms would be put in place to ensure direct reporting of probable adverse events to the investigator by patients (via telephone, which will be available 24 h on all days)During follow-up visits, probable adverse events will be noted by history and examination and investigated upon in detail. The attending physician will assess for any symptoms and signs of the potential side effects. All adverse effects observed will be documented in the Case Record Form (CRF)All serious adverse events will be reported to the Ethics Review Committee (ERC), Faculty of Medicine, University of Colombo, and the National Pharmaco-vigilance Unit of the Department of Pharmacology, Faculty of Medicine, University of ColomboAn independent Data Safety Monitoring Board (DSMB), consisting of clinical pharmacologists, physicians and members of the ERC, will evaluate all adverse events at regular intervalsTermination of study: in the event of major adverse effects occurring in a significant proportion of the study population the study would be terminated pending further investigation

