## Methods/design

### Objectives and hypothesis

Hypothesis: blood pressure in patients with resistant hypertension treated with propranolol will be lower than that of the control group.

Primary objective: the study aims to compare the safety and efficacy of propranolol in patients with resistant hypertension when added to a multidrug combination (at least three drugs) consisting of a diuretic and an angiotensin-converting enzyme inhibitor (ACEI)/angiotensin-II receptor blocker (ARB), a centrally acting drug, and an alpha blocker or calcium channel blocker.

Secondary objectives: (1) to describe the sociodemographic and clinical characteristics of patients with resistant hypertension at baseline, (2) to describe the complications and cardiovascular risk associations of patients with resistant hypertension at baseline, (c) to describe the impact of propranolol administration on serum/urinary electrolytes and oxidative stress in patients with resistant hypertension and (4) to assess sodium excretion in patients with resistant hypertension at baseline and following propranolol therapy.

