### Blinding

The study drugs are double blinded to both investigators and subjects. The drug manufacturing will be done by Astron Lanka (PVT) Ltd., Colombo, Sri Lanka, and they will be responsible for the labeling of the capsules with code numbers.

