After randomization patients will enter the clinical trial and will be given either propranolol 40 mg three times a day or a placebo which will be added to the patients’ routine medication. At the first two follow-up visits (visits 1 and 2) the following examinations and investigations will be performed: pulse rate and blood pressure measurements (as detailed above), measurements of serum sodium, potassium, urea and creatinine levels and an electrocardiogram. During the follow-up visits, if blood pressure is not controlled both drug and placebo dose will be doubled once (maximum dose of propranolol used in this study will be 80 mg three times daily). Three months after initiation of the drug, final examination of the patients will be carried out (visit 3), as described in Fig. 2.

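### Adverse-event collection is worded in causal terms, so non-serious events not suspected to be drug-related may go unrecorded in a trial that compares safety between arms

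*Protocol article*

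**What the plan says.** All places are in the Protocol article.

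- **Adverse effect evaluation** lists known effects of propranolol and then sets out what happens when a probable adverse reaction occurs.
  - Telephone reporting: "mechanisms would be put in place to ensure direct reporting of probable adverse events to the investigator by patients".
  - Visits: "During follow-up visits, probable adverse events will be noted by history and examination and investigated upon in detail".
  - Physician: "The attending physician will assess for any symptoms and signs of the potential side effects".
  - Recording: "All adverse effects observed will be documented in the Case Record Form (CRF".
  - Serious events: "All serious adverse events will be reported to the Ethics Review Committee (ERC", and also to the national pharmacovigilance unit. No causality condition is attached.
  - DSMB: it is to review all adverse events periodically, again with no causality condition.
- **Objectives and hypothesis**: "the study aims to compare the safety and efficacy of propranolol in patients with resistant hypertension".
- **Outcomes** makes safety a between-group secondary outcome. Serious adverse effects are named as included, so the outcome is not limited to them.
- **Blinding**: "The study drugs are double blinded to both investigators and subjects".
- **Study schedule** gives the examinations at visits 1 and 2: "pulse rate and blood pressure measurements (as detailed above), measurements of serum sodium, potassium, urea and creatinine levels and an electrocardiogram".

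**The concern.** A between-arm safety comparison works best when every untoward event is recorded in both arms and relatedness is judged afterwards. The placebo arm then supplies the background rate, and the difference between arms shows what the drug does. If relatedness is judged before recording, that judgement replaces the comparison. The events most easily lost are those nobody expects of the drug, and these are the ones a randomised comparison is best placed to reveal.

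At stake is the completeness of the non-serious safety data. These data fall within the safety part of the primary objective and within the safety secondary outcome. Events not noted at the time cannot be reliably recovered later.

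**Working it through.** **1. The wording, side by side.** No figure in the plan is in dispute, so the main check is of the text.

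| Step | What it covers | Tied to suspected cause? |
|---|---|---|
| Telephone reports | events called probable | yes |
| Noting at visits | events called probable | yes |
| Physician's assessment | potential side effects | yes |
| CRF entry | all adverse effects observed | partly: no 'probable' filter, but 'effect' is a causal word |
| Serious event reporting | all serious adverse events | no |
| DSMB review | all adverse events | no |

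The first four rows feed the last. For non-serious events, no stated step collects everything the DSMB is to review. That is an inconsistency within one section.

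**2. What equal under-recording costs.** Inputs from the document: 200 patients allocated 1:1, so about 100 per arm (Sample size), and a two-sided 0.05 level. Assumed, because the document gives no adverse-event rates: true risks p1 = 40% and p2 = 20%, and a capture fraction c that is the same in both arms. Observed risks are c·p1 and c·p2. Write q1 = c·p1, q2 = c·p2 and q for their mean. Then

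power = Φ{ [ (q1 − q2) − 1.96·√(2q(1 − q)/n) ] / √( [q1(1 − q1) + q2(1 − q2)]/n ) }, with n = 100.

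| c | observed risks | difference | ratio | power |
|---|---|---|---|---|
| 1.00 | 40% v 20% | 20 points | 2.0 | 88% |
| 0.75 | 30% v 15% | 15 points | 2.0 | 72% |
| 0.50 | 20% v 10% | 10 points | 2.0 | 51% |

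For c = 0.75: (0.15 − 1.96 × 0.0591)/0.0581 = 0.59, and Φ(0.59) = 0.72. Equal under-recording shrinks the difference and costs power but leaves the ratio unchanged.

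**3. What unequal under-recording would do.** Assume a true risk of 20% in both arms, so there is no drug effect.

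- Capture 60% v 50%: 0.20 × 0.60 = 12% v 0.20 × 0.50 = 10%, ratio 1.2.
- Capture 80% v 50%: 16% v 10%, ratio 1.6.
- Capture 90% in patients with a slow pulse and 60% in the rest, with slow pulse in 60% of the propranolol arm and 10% of the placebo arm: 0.6 × 0.9 + 0.4 × 0.6 = 0.78 v 0.1 × 0.9 + 0.9 × 0.6 = 0.63, ratio 0.78/0.63 = 1.24.

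These show what would follow if recording differed by arm. Nothing in the document shows that it would.

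**The case against.** The strongest reply is that the text is loose rather than restrictive.

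- **The section uses its terms interchangeably.** Reaction, event, effect and side effect are mixed, and patients who telephone are not grading causality, so 'probable' may only mean suspected. At visits, events are noted and then investigated, which suggests that noting comes first. This stands as a reading. But 'suspected' is still a causal condition, and an ambiguous word will be applied differently by different staff.
- **A reader might infer that events are captured only if judged probable.** The text does not say so. The word 'only' is absent, the CRF sentence has no 'probable' filter, and no sentence says that unrelated events are dropped. Serious adverse events, the one safety item that Outcomes names, are all reported. The point is therefore confined to non-serious events.
- **A reader might infer that the list of propranolol effects is a checklist, and that acute coronary syndrome and stroke are not sought because they are not on it.** The list is a description of the drug. Both events are secondary outcomes and would ordinarily be serious. The items for each visit are in Fig. 2, which is not available here, so no missing step can be claimed.
- **A reader might infer a biased comparison.** The trial is double-blind and the same assessment applies to both arms. Differential recording would need something to suggest the arm, such as the pulse rate or ECG taken at visits 1 and 2. That is possible in any beta-blocker trial but is not shown here. Pulse, ECG, electrolytes, urea and creatinine are also measured whatever anyone suspects, so harms visible in them do not depend on this wording.
- **The full protocol or operating procedures may define adverse events properly.** They may, and missing definitions are no finding in a condensed article. The point rests on what the article states: collection sentences narrower than the DSMB's remit.

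**Conclusion.** The point holds in limited form. The collection wording is causal, it is inconsistent with the DSMB's remit in the same section, and it is poorly suited to a trial that compares safety between arms. Read literally, non-serious events not suspected to be drug-related may go unrecorded, so that part of the safety comparison may be incomplete and an unexpected harm may be missed.

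The size cannot be fixed from the document. Under the assumed risks, equal capture of between 75% and 50% lowers power from 88% to between 72% and 51%. The ratios of 1.2 to 1.6 need unequal capture, which is possible but not demonstrated. The wording does not make the safety objective unanswerable. It should be corrected, and the Trial status section says enrolment had not begun.

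**What to change.** Reword Adverse effect evaluation so that:

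1. every untoward event from the first capsule to visit 3 is recorded in the CRF, in both arms, regardless of suspected cause;
2. events are elicited in the same way in both arms at each follow-up visit;
3. causality is judged blind to allocation, after recording, and entered as a separate CRF field;
4. the between-arm comparison uses all recorded events, with those suspected to be drug-related shown as a subset.

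The collection sentences would then match what the DSMB is to review. If the full protocol already says this, the article's wording need only be aligned with it.

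The cost is a protocol and CRF wording change, slightly longer history-taking at existing visits, and more minor events to enter. No extra visits or patients are needed.
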